### **4. Compare the pCRM involvement rate in the control versus intervention arm**

The overall pCRM involvement rate between the control and intervention arms will be assessed according to an intention to treat analysis. This will be important for assessing the safety of the mrTRG directed approach. We hypothesise that a greater proportion of downstaging in the intervention arm will result in relative reduction in the overall rate of pCRM involvement compared with the control arm. The rate of inoperable regrowth occurring in patients that are managed by deferral of surgery will be specifically considered.

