### **8.2.2 PROCEDURE IF A LOCAL REGROWTH IS DETECTED**

Patients with evidence of clinical or radiological local regrowth or pelvic relapse must be treated at least as urgently as a primary rectal cancer by the surgical team. Refer to suspected regrowth pathway in Section 8.2.3 below. Complete a **SURVEILLANCE CRF**. If patient proceeds to surgery Follow-up and CRF completion should be carried out according to the Control arm (Section 10.1, Assessment Schedule Control Arm and Section 11.1, Post-Surgery Follow Up). The **SURGERY, SURGICAL MORBIDITY** and **PATHOLOGY REPORTING Forms** should be completed when the patient undergoes surgery. If the colorectal MDT decision is to offer adjuvant therapy then the **CHEMOTHERAPY** and **TOXICITY Forms** should also be completed during treatment. The timing of the oncological outcomes, assessment of late surgical complications and PROMs should be completed as per protocol.

If patient refuses surgery or is not fit for surgery then a **DISCONTINUATION OF TRIAL TREATMENT Form** should be completed and the patient followed-up unless they withdraw consent to further data collection.

The patient is still eligible for analysis on an intention to treat basis.

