### 11.3 DEFINITIONS REQUIRED FOR FOLLOW-UP

**Complete response** is defined as undetectable disease at the site of the primary tumour following pre-operative chemotherapy and/or radiotherapy. A pre-fix to denote the mode of assessment must also be included - clinical (c), MRI (mr) and pathology (p).

**Disease recurrence** is defined as either evidence of loco-regional recurrence or established metastatic disease. The time to the event is measured from the start of chemoradiotherapy to the date of the diagnostic investigation or MDT.

**Regrowth** is defined as the first recorded evidence of disease at the site of the primary tumour, in a patient with previous investigations suggesting an apparent complete response or undetectable disease (mrTRG1&2). The terms 'early regrowth' and 'late regrowth' will not be used in the trial.

**Unsalvageable regrowth** is defined as a tumour with radiological evidence of a good response that is initially managed by deferral of surgery but progresses. The extent of progression means that pCRM involvement becomes inevitable and so surgery is not performed, or pCRM involvement occurs when surgery is attempted.

**Loco-regional recurrence** (one of):

- Clinical recurrence with biopsy proof of recurrence
- CEA elevation and enlarging or new mass (includes pelvic, nodal and peritoneal disease). Biopsy confirmation is contraindicated or not feasible
- CEA non-secretors: enlarging or new mass (includes pelvic, nodal and peritoneal disease). Biopsy confirmation is contraindicated or not feasible (with or without PET/CT confirmation)

**Distant Metastases** (one of):

- This is defined as any confirmed evidence of disease above the L5/S1 junction
- Clinical recurrence with biopsy proof of recurrence
- CEA elevation and evidence of distant metastases. Biopsy confirmation is contraindicated or not feasible

- CEA non-secretors: evidence of distant metastases. Biopsy confirmation is contraindicated or not feasible (with or without PET/CT confirmation). Initial report to Trials Unit should define this as SUSPECTED. A further report 6 months later should define this as CONFIRMED if supported by MDT review.

***Inoperable Disease*** (one of):

- MDT decision that the local extent of disease on the post CRT pelvic MRI is not resectable
- At laparotomy the local extent of disease is not resectable

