| NBOCAP                 | National Bowel Cancer Audit Programme                                                                                                                                                                                                                                                                                                                                                                                                                                                                              |
| pCRM involvement       | pCRM – pathological circumferential resection margin. pCRM involvement is defined as tumour ≤ 1mm from the circumferential resection margin at histopathological analysis. For the purpose of the trial, if a patient in the deferral of surgery arm does not undergo an operation and remains 'regrowth' free at 3-year follow-up this will also be defined as pCRM negative.                                                                                                                                     |
| QoL                    | Quality of Life                                                                                                                                                                                                                                                                                                                                                                                                                                                                                                    |
| RCT                    | Randomised Control Trial                                                                                                                                                                                                                                                                                                                                                                                                                                                                                           |

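### The pCRM definition scores unoperated deferral successes as negative but gives unoperated local failures no score, so the intention-to-treat pCRM rate is one-sided

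*Protocol*

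**What the plan says.** Protocol section 17 ties the event to a specimen: "pCRM involvement is defined as tumour ≤ 1mm from the circumferential resection margin at histopathological analysis". It then adds one imputation. This concerns the deferral patient who is never operated on and stays clear of regrowth, and its wording ends: "free at 3-year follow-up this will also be defined as pCRM negative".

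Two other sections describe deferral patients who have regrowth and no specimen:

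- Section 11.3 defines unsalvageable regrowth as progression after deferral such that "pCRM involvement becomes inevitable and so surgery is not performed, or pCRM involvement occurs when surgery is attempted". The first branch has no resection. The same section defines inoperable disease, which includes an MDT decision on the post-CRT MRI that the local disease cannot be resected.
- Section 8.2.2, on detected regrowth, provides for the unoperated case: "If patient refuses surgery or is not fit for surgery", a discontinuation form is completed, follow-up continues, and the patient stays eligible for intention-to-treat analysis.

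Section 4.2, objective 4, sets the analysis: "The overall pCRM involvement rate between the control and intervention arms will be assessed according to an intention to treat analysis". It calls this important for judging the safety of the strategy and expects that more downstaging "will result in relative reduction in the overall rate of pCRM involvement compared with the control arm". It adds that inoperable regrowth after deferral will be specifically considered.

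Section 14.2.2 lists the pCRM rate and the proportion with unsalvageable regrowth as separate items, each compared by Fisher's exact test. It repeats the pCRM comparison among good responders. Unsalvageable regrowth above 5% may close the trial or stop progression to phase III.

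**The concern.** An intention-to-treat rate needs an outcome value for every randomised patient. Section 17 supplies one for the unoperated patient who does well and none for the unoperated patient who does badly. The first adds a negative to the denominator. The second has neither a specimen nor regrowth-free status, and so has no pCRM value.

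The good outcomes of deferral therefore enter the rate, while its worst local outcomes do not. Deferral belongs to the intervention arm only, so the imputed negatives and the deferral-specific failures all fall there. A lower pCRM rate in that arm is what section 4.2 hypothesises, and part of it could come from the scoring rule. Section 14.2.2 uses the secondary endpoints to inform the phase III design, and section 3.1 carries feasibility patients into the phase III analysis.

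**Working it through.** The protocol states no pCRM rate and no power for this comparison, so there is no figure of its own to reproduce.

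**Inputs from the protocol.** Planned sample size 90 (Trial Summary) and 2:1 allocation (section 3.2) give 60 intervention and 30 control patients. The Introduction says that up to 30% have a complete or near complete response; 30% of 60 is 18.

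**Assumptions.** 18 of 60 defer and 42 are operated on. pCRM involvement among operated patients is 10%, giving 4 in the intervention arm (0.10 × 42 = 4.2) and 3 of 30 in control. No deferred patient has salvage surgery with an involved margin. No control patient is unscored. Let u be the number of unresected deferral failures.

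**Formulas.** As written, reading an unscored patient as absent from the rate: 4/(60 − u). With failures counted as involved: (4 + u)/60.

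| u | As written | Failures counted | Control |
|---|---|---|---|
| 1 | 4/59 = 6.8% | 5/60 = 8.3% | 10.0% |
| 2 | 4/58 = 6.9% | 6/60 = 10.0% | 10.0% |
| 3 | 4/57 = 7.0% | 7/60 = 11.7% | 10.0% |
| 4 | 4/56 = 7.1% | 8/60 = 13.3% | 10.0% |

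At u = 2 the apparent relative reduction is 1 − 6.9/10.0 = 31%, and it vanishes when the failures are counted. At u = 3 the direction changes.

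**Range over the deferral share.** With 30%, 40% or 50% deferring, 5% or 10% of deferrals ending as unresected local failure, and unrounded expected counts, the intervention rate is 5.1% to 7.2% as written and 7.5% to 10.0% with failures counted. For example, at 50% and 10%: 3/57 = 5.3% against 6/60 = 10.0%.

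**Deferred good responders.** If no operated patient among the 18 has an involved margin, u = 2 reads 0/16 = 0% as written and 2/18 = 11.1% with failures counted.

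**Unscored control patients.** Section 11.3 and Appendix 4 allow inoperable disease in the control arm too. Keep 4 involved margins and u = 2 in the intervention arm and 3 involved margins in control:

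| Unscored in control | As written | Ratio | Failures counted | Ratio |
|---|---|---|---|---|
| 0 | 4/58 v 3/30 | 0.69 | 6/60 v 3/30 | 1.00 |
| 1 | 4/58 v 3/29 | 0.67 | 6/60 v 4/30 | 0.75 |
| 2 | 4/58 v 3/28 | 0.64 | 6/60 v 5/30 | 0.60 |

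Control is half the size, so each unscored control patient weighs about twice as much. One nearly cancels the distortion, and two reverse it.

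**Test result.** At u = 2 with no unscored control patients, Fisher's exact p is 0.69 as written and 1.00 with failures counted. The rule changes the estimate and not a formal decision.

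**The case against.** Three arguments stand against a stronger reading.

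1. A reader might infer that the protocol excludes these patients or hides them. It does neither. No passage removes them from the pCRM denominator; 8.2.2 and section 11 keep them evaluable, and their score is simply left open. Unsalvageable regrowth is tested in its own right in 14.2.2, carries the 5% alert, and is recorded as an adverse event of deferral (Appendix 1, section 2). In the worked case, 2 failures among 18 to 30 deferring patients are 11.1% to 6.7%, above the alert level if deferring patients are the denominator. On all 60 they would be 3.3%; the denominator is not spelled out.
2. A reader might infer that the rule always favours the intervention arm. The control-arm table shows otherwise.
3. A statistical analysis plan may settle the scoring. That would excuse a missing detail. Here, though, the protocol has already fixed half of the rule.

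The first argument stands as to safety reporting but does not repair the pCRM rate. The unsalvageable-regrowth endpoint pools unoperated cases with operated involved margins that the pCRM rate already counts, so the two rates cannot be added. It concerns deferred patients only. Regrowth left unoperated through refusal or unfitness may meet neither definition.

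**Conclusion.** Wrong as written, of moderate severity. Section 17 imputes only the good unoperated outcome, in a comparison that section 4.2 declares to be intention to treat. The likely effect is a lower intervention-arm rate: 6.9% instead of 10.0% in the worked case, and 5.1% to 7.2% instead of 7.5% to 10.0% across the range. All of these rest on assumed pCRM and failure rates and on no unscored control patients. With two unscored control patients the ratio is 0.64 as written against 0.60 counted, so the direction is likely but not certain.

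It would go too far to treat this as a threat to the trial's main conclusion. The primary endpoint is recruitment, and the pCRM comparison is secondary and exploratory. Scoring the regrowth-free patient as negative is reasonable in itself; the fault is the missing counterpart.

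**What to change.** In sections 17 and 14.2.2, define the comparison over all randomised patients as pCRM involvement or unresected local disease:

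- Count unoperated unsalvageable regrowth and inoperable disease, both as defined in 11.3, as involved in either arm.
- Show regrowth left unoperated through refusal or unfitness on a separate line, and count it as involved in a sensitivity analysis.
- Use the same definition for the good-responder comparison.
- Keep unsalvageable regrowth as its own endpoint.

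The cost is a change of wording in two sections. No new data are needed: the protocol already has regrowth recorded on the SURVEILLANCE Form, unsalvageable regrowth on the ADVERSE EVENT Form, and refusal or unfitness on the DISCONTINUATION OF TRIAL TREATMENT Form. Patient management does not change. The downside is that the reported rates become slightly less favourable.

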## APPENDIX 1: SAFETY MONITORING PROCEDURES

### 1. DEFINITIONS

#### 1.1. ADVERSE EVENTS

An adverse event is any untoward medical occurrence in a patient or clinical investigation subject administered a pharmaceutical product and that does not necessarily have a causal relationship with this treatment.

Worsening of a pre-existing medical condition (e.g. diabetes, migraine headaches, gout) should be considered an adverse event if there is either an increase in severity, frequency, or duration of the condition or an association with significantly worse outcomes. Interventions for pre-existing conditions (e.g., elective cosmetic surgery) or medical procedures that were planned before study enrolment are not considered adverse events.

The investigator is responsible for reviewing laboratory test results and determining whether an abnormal value in an individual study patient represents a change from values before the study. In general, abnormal laboratory findings without clinical significance (based on the investigator's judgment) should not be recorded as adverse events; however, laboratory value changes requiring therapy or adjustment in prior therapy are considered adverse events.

#### 1.2 ADVERSE REACTION (AR)

All untoward and unintended responses to chemotherapy or radiotherapy related to any dose administered to that subject. A causal relationship between a trial treatment and an adverse event is at least a reasonable possibility, i.e. the relationship cannot be ruled out.

#### 1.3 UNEXPECTED ADVERSE REACTION (UAR)

An adverse reaction the nature and severity of which is not consistent with the information about the medicinal product in question set out in the Summary of Product Characteristics (SmPC) for that product.

#### 1.4 SERIOUS ADVERSE EVENT (SAE)

Any adverse event, adverse reaction or unexpected adverse reaction which:

- Results in death
- Is life-threatening (the patient was at risk of death at the time of the event). This does not refer to an event that hypothetically might have caused death if it were more severe.
- Requires in-patient hospitalisation or prolongs existing hospitalisation.
- Results in persistent or significant disability/incapacity

- Consists of a congenital abnormality or birth defect

#### **1.4.1 DISEASE-RELATED EVENTS**

Elective hospital admissions for procedures related to the study treatment, for example administration of chemotherapy, or central line insertion, or elective admissions to simplify treatment are exempt from being reported as SAEs.

#### **1.4.2 IMPORTANT MEDICAL EVENTS**

Events that may not immediately life-threatening or result in death or hospitalisation but may jeopardise the patient or may require intervention to prevent one of the other outcomes listed in the definition of an SAE above should also be considered serious.

#### **1.5 SERIOUS ADVERSE REACTION (SAR)**

An SAE where a causal relationship between the investigational medicinal product (the systemic chemotherapy) and the SAE is at least a reasonable possibility, i.e., the relationship cannot be ruled out.

#### **1.6 SUSPECTED UNEXPECTED SERIOUS ADVERSE REACTION (SUSAR)**

A SUSAR is defined as an adverse reaction suspected to be related to the investigational medical product (the systemic chemotherapy) that is both unexpected and serious.

## **2 REPORTING PROCEDURES FOR ALL ADVERSE EVENTS**

The investigator is responsible for ensuring that all adverse events (including SAEs) observed by the investigator or reported by patients from the date of the post-CRT MRI scan is performed until 30 days after the last dose of chemotherapy is administered are properly captured in the patients' medical records (source documents). Adverse events occurring in all arms of the trial should be reported with the same diligence so that bias is not introduced to the apparent incidence of adverse events observed in the intervention arm. In addition, the investigator is responsible for ensuring that, for those patients randomised, all adverse events captured on the patients' medical records (as specified above) are reported on the CRF.

**NOTE: The rationale for commencing AE recording from the date of the post-CRT MRI rather than the date of randomization is to avoid capturing AEs during and shortly after the last two weeks of CRT i.e. those that could be possibly related to CRT rather than the IMP(s) (systemic chemotherapy) received as part of the trial, which patients do not receive until after the post-CRT MRI scan is performed 4-6 weeks after the completion of CRT.**

As per assessment schedules residual toxicity will be assessed at the 12 month clinic visit.

In the TRIGGER trial, the seriousness, causality and expectedness of all adverse events will be assessed by the principal investigator (or delegate) at the participating site. Upon receipt at the trial management centre, all SAEs will be also reviewed by the Chief Investigator and CTIMP Lead at the Royal Marsden (or delegate).

## **ADVERSE EVENTS AND SERIOUS ADVERSE EVENTS RELATED TO SURGERY**

Surgical adverse events and serious adverse events have been translated into complications. As surgery takes place during the Intervention Phase of the trial adverse events related to surgery should also be recorded on the **ADVERSE EVENTS Form**. Investigators should record on the **ADVERSE EVENT Form** whether the AE is related to systemic chemotherapy or surgery. A list of expected surgical complications is included in Section 2.3 below. Further information relating to early and late surgical complications will be captured on the **SURGICAL MORBIDITY Form**.

Please see section 2.1.4 regarding reporting of involved surgical resection margins (pCRM involvement).

For deferral of surgery the only adverse event of interest is **unsalvageable regrowth** (definition in section 11.3). This will be detected by the MDT during follow up. If it occurs this should be recorded on the **ADVERSE EVENT Form** and it is *definitely related* to deferral of surgery. A **SURVEILLANCE Form** should also be completed.

## **2.1 DEFINING THE ADVERSE EVENT**

An adverse event term must be provided for each adverse event, preferably using the term listed in the Common Terminology Criteria for Adverse Events (CTCAE) v4.0, available online at:

[http://evs.nci.nih.gov/ftp1/CTCAE/CTCAE\\_4.03\\_2010-06-14\\_QuickReference\\_5x7.pdf](http://evs.nci.nih.gov/ftp1/CTCAE/CTCAE_4.03_2010-06-14_QuickReference_5x7.pdf)

### **2.1.1 DETERMINING ADVERSE EVENT SEVERITY**

The NCI CTCAE version 4.0 must be used to grade each AE, and the worst grade recorded.

In those cases where the CTCAE criteria do not apply, severity should be coded according to the following criteria:

- 1 = Mild (awareness of sign or symptom, but easily tolerated)
- 2 = Moderate (discomfort enough to cause interference with normal daily activities)
- 3 = Severe (inability to perform normal daily activities)
- 4 = Life threatening (immediate risk of death from the reaction as it occurred)
- 5 = Fatal (the event resulted in death)

### 2.1.2 DETERMINING ADVERSE EVENT SERIOUSNESS

An adverse event is deemed serious if it satisfies any of the criteria in section 1.4 of this appendix above.

### 2.1.3 DETERMINING ADVERSE EVENT CAUSALITY

We are including adverse events for surgery and deferral of surgery (see section 2 above) as well as for the administration of systemic chemotherapy. For the IMP (systemic chemotherapy) causality should be assessed as follows:

|                        |                                                                                                                                                                                      |
|------------------------|--------------------------------------------------------------------------------------------------------------------------------------------------------------------------------------|
| Unrelated              | The AE is definitely not associated with the systemic chemotherapy administered.                                                                                                     |
| Unlikely to be related | The time association or the patient's clinical state is such that the systemic chemotherapy is not likely to have had an association with the observed effect.                       |
| Possibly related       | Starts within a time related to the systemic chemotherapy administration and
A causal relationship between systemic chemotherapy and the AE is at least a reasonable possibility. |
| Probably related       | Starts within a time related to the systemic chemotherapy administration and
Cannot be reasonably explained by known characteristics of the patient's clinical state.             |
| Definitely related     | Starts within a time related to the systemic chemotherapy administration and
No obvious alternative medical explanation.                                                          |

**Note:** *Drug-related refers to events assessed as possible, probable or definitely.*

### 2.1.4 ADVERSE EVENTS OF SPECIAL INTEREST

These chemotherapy agents are established treatments for colorectal cancer, therefore there are no IMP-related events of special interest.

**All involved surgical resection margins (pCRM involvement) should be treated as adverse events of special interest requiring expedited reporting to the trial office. Information relating to pCRM involvement is captured on the PATHOLOGY CRF, which should be completed at the time the surgical specimen is evaluated and reported. The PATHOLOGY CRF should then be sent to the TRIGGER Trial office as soon as it has been completed and signed and dated by the local Pathologist.**

